### Area-Level Health Data

Publicly available data on vaccination coverage and healthcare utilization will be obtained from the Chicago Data Portal and the Illinois Department of Public Health [33, 34]. These data will be used to assess changes in vaccination coverage over time as clusters transition from control to intervention conditions. Exploratory analyses will also examine area-level influenza-like illness, hospitalizations, and emergency department utilization during the campaign period.

### Sample Size

The primary outcome will be vaccination-related decision-making among members of promotores’ social media networks, including willingness to receive recommended immunizations or recommend them to others.

Sample size estimates were informed by prior studies reporting vaccination coverage ranging from 33.1% to 45.4% in urban populations served by Spanish-speaking community health initiatives [33, 35]. Using these estimates, we calculated the required sample size for a paired design with a two-sided α of 0.05, 80% power, a relative risk of 1.5, and an assumed within-participant correlation coefficient of 0.25. We then applied the approach described by Hemming and Taljaard to account for the stepped-wedge cluster design, incorporating four steps, variable cluster sizes, and an intracluster correlation coefficient of 0.01 [36]. Design effect adjustments were applied to estimate overall and per-cluster sample size requirements.

Based on these calculations, we will recruit a minimum of 35 promotores across seven neighborhoods, organized into four clusters. Under the planned four-step rollout, clusters will sequentially transition from control to intervention conditions at six-month intervals. This sample size will provide 80% power to detect a meaningful difference in vaccination-related decision-making over time, corresponding to an increase from 45% at baseline to 68% during the intervention phase. To achieve adequate power, each promotor will recruit approximately 45 members of their social media network to complete baseline and follow-up surveys.

### Data Analysis

Analyses will be conducted to characterize social media practices, evaluate engagement with the training program, and assess the effectiveness of communication strategies over time. All analyses will account for the stepped-wedge cluster design and repeated measures within participants and clusters.

### Surveys

Descriptive data will summarize participant characteristics, social media use patterns, and baseline measures using appropriate summary statistics. Categorical variables will be reported as counts and percentages, and sparse categories will be combined where appropriate. Continuous variables will be assessed for distributional assumptions and summarized as means with standard deviations or medians with interquartile ranges.

Changes in survey-based outcomes, including knowledge, confidence in applying science communication principles, and vaccination-related decision-making, will be evaluated using generalized linear mixed models (GLMMs). These models will account for clustering at the promotor and neighborhood levels and will include fixed effects for time and intervention status. Relevant demographic and contextual covariates (e.g., age, primary language, and zip code) will be included as appropriate.

Repeated measures analyses will be used to assess changes over time across baseline, 6-months, and post-campaign assessments. Binary outcomes will be analyzed using logistic mixed-effects models, while continuous and ordinal outcomes will be analyzed using linear or cumulative link mixed models, depending on distributional assumptions.

### Focus Groups

Qualitative data from focus groups will be analyzed using the constant comparative method [37]. Transcripts will be coded iteratively, with an initial subset independently coded by multiple researchers to develop a preliminary codebook, followed by independent coding of the remaining transcripts. Discrepancies will be resolved through consensus, and themes will be refined using representative quotations. Data collection and analysis will continue until thematic saturation is achieved; if saturation is not reached, additional interviews may be conducted. Findings will be reported in accordance with the Standards for Reporting Qualitative Research [38].

### Social Media Engagement

Social media engagement will be quantified using platform-derived metrics, including impressions, likes, comments, and shares. Count-based outcomes will be analyzed using Poisson or negative binomial regression models, as appropriate based on dispersion characteristics. Continuous or ordinal survey outcomes will be analyzed using linear or cumulative link mixed models, depending on distributional assumptions. Repeated measures of generalized linear mixed models will be used to assess changes in engagement over time while accounting for clustering within promotores and neighborhood clusters under the stepped-wedge design.

Characteristics of social media posts and audience responses will be extracted using large-language models and multimodal analytic approaches applied to text, images, and video content. These characteristics will include sentiment, discussion of personal experience, presence of scientific evidence, and patterns of agreement or disagreement. These features will be incorporated as independent variables in regression and machine learning–based predictive models to examine their association with engagement outcomes and to identify characteristics of posts associated with higher levels of interaction within promotores’ social networks.

In addition to quantifying the volume of engagement, analyses will examine the nature of engagement by evaluating the content of audience responses to promotores’ posts. These analyses will provide insight into how different types of communication strategies influence both the extent and quality of interaction.

Implementation fidelity will be assessed by quantifying the number and characteristics of posts produced, including adherence to training principles such as inclusion of credible sources and use of narrative elements.

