### Intervention

The Dime La VerDAD intervention will be a structured, community-engaged social media training program designed to support promotores de salud in disseminating reliable, evidence-based information about respiratory virus prevention within their social media networks. The program will be grounded in principles of health communication and will focus on building practical skills in identifying inaccurate health claims, evaluating information sources, and developing clear and accessible health messages.

The curriculum will include training in infographic design, assessment of source credibility, and strategies for communicating effectively across diverse audiences. Participants will be guided in incorporating personal narratives into their social media posts and in responding constructively to disagreement in online environments. As part of the program, promotores will also develop original social media content, including infographics and accompanying captions, and will share these posts within their existing social media networks. Content will be iteratively refined through structured feedback from instructors and peers. A detailed outline of session topics, activities, and assignments is provided in Table 1.

The intervention will be delivered through a series of structured training sessions led by bilingual instructors. Sessions will be conducted in a hybrid format, with options for in-person or virtual participation, and will be supplemented by independent work focused on content development and social media engagement. Across the program, each cohort will complete approximately 18 hours of structured training.

To support adherence and minimize attrition, the study will implement a multi-pronged retention strategy that accounts for potential barriers such as scheduling constraints, competing work responsibilities, and other personal obligations. This approach will include flexible scheduling to accommodate participants’ availability, regular reminder communications regarding study activities, and financial compensation for participation.

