### Social Media Engagement

Social media data will be collected from platforms commonly used within participants’ networks, including Facebook and Instagram. Promotores will be trained to export data from their posts (e.g., Facebook JSON exports) and share these files with the research team. For platforms that do not support direct data export, alternative approaches will be used, including participant-reported metrics or researcher access to social media groups or communication channels, as appropriate.

Engagement metrics will include impressions (i.e., number of users who view a post) and indicators of interaction such as likes, comments, and shares. In addition, the content of promotores’ posts and associated audience responses will be analyzed to characterize features of communication, including sentiment, use of personal narratives, and incorporation of scientific evidence. These measures will be used to examine how characteristics of social media content relate to engagement within promotores’ networks.

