## Figures and Tables

**Figure 1 F1:**
[figure not shown]
Geographically distinct community areas used for the recruitment of promotores.

**Table 1 T1:** Dime La VerDAD curriculum structure.

Session	Topic	Details	Homework
Focus Group	Baseline Discussion	Structured discussion to understand current social media practices, commonly encountered health claims, and communication experiences	
1	Designing Infographics	Introduction to infographics and visual communication principles; overview of Canva tools	• Join the study communication group (on WhatsApp) • Friend/follow *Dime La VerDAD* on social media platforms • Access the Canva folder • Share 2–3 practice posts on social media
2	Understanding Inaccurate Health Claims	Overview of different types of inaccurate health information and how it circulates online; discussion of potential impacts	• Invite approximately 45 social media network members to complete the pre-survey • Identify one vaccine-related health claim to address ○ Locate 2–3 credible sources • Begin drafting an infographic in Canva
3	Communicating Across Audiences	Principles of effective communication and audience engagement	• Develop draft infographics (1 Facebook, 1 Instagram) ○ Include a link to a credible resource • Draft a caption incorporating a personal narrative ○ Include (2–3) relevant hashtags and tags as appropriate
4	Evaluating Source Credibility	Methods for assessing the reliability of online sources (e.g., SIFT method, fact-checking tools)	• Verify sources using structured evaluation methods ○ Identify additional credible resources if needed • Revise draft infographic and caption based on instructor and cohort participant feedback
5	Applying Science Communication Strategies	Strategies for making evidence-based messages engaging and understandable	• Refine your infographic and caption based on feedback • Post standardized informational content provided by the study team
6	Responding to Disagreement on Social Media	Approaches to addressing dissent constructively and maintaining professionalism online	• Develop a strategy to address responses from people with opposing views • Present final infographic and communication strategy • Post standardized informational content provided by the study team • Post your finalized infographic and caption • Six months after baseline focus group, invite social media network members to complete the post-survey

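### The comment count used as an engagement outcome is not limited to audience members, so promotores' own replies, which the training targets, may raise it after crossover

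*Protocol article*

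**What the plan says.** The Outcomes part of the protocol article, under Social Media Engagement, defines the measures: "Engagement metrics will include impressions (i.e., number of users who view a post) and indicators of interaction such as likes, comments, and shares". The data come from the promotores themselves: "Promotores will be trained to export data from their posts (e.g., Facebook JSON exports) and share these files with the research team". Where a platform has no export, participant-reported figures or researcher access to the channel are used instead. The Data Analysis part repeats the scoring rule ("Social media engagement will be quantified using platform-derived metrics, including impressions, likes, comments, and shares") and gives the model: "Count-based outcomes will be analyzed using Poisson or negative binomial regression models, as appropriate based on dispersion characteristics". Mixed models then estimate change over the stepped-wedge rollout, with clustering by promotor and neighborhood. The content of audience responses is analysed as well, in addition to the volume counts and not in place of them.

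The Intervention section lists among the skills taught "responding constructively to disagreement in online environments". The Session 6 homework in Table 1 includes "Develop a strategy to address responses from people with opposing views". Under Study Design, promotores in the control phase carry on as before, with no training or guidance from the study team.

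**The concern.** Both Social Media Engagement sections make clear that the quantity of interest is how the promotor's network responds. The scoring rule takes comments from anyone, and that includes the person who wrote the post. The training addresses how promotores answer commenters, and it reaches each cluster only at crossover. A behaviour taught by the intervention can therefore enter an outcome meant to reflect the audience, and can do so more in one phase than in the other.

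The planned model does not remove this. Fixed effects for time absorb calendar trends, random effects absorb stable differences between promotores and neighborhoods, and the negative binomial dispersion parameter affects the variance only. A shift in own replies that begins with the training coincides with intervention status and is estimated as part of the intervention effect.

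Engagement is not the primary outcome, but the Abstract names it among the primary and secondary outcomes and the Background states a hypothesis about it. A misleading comment result would therefore bear on a stated aim.

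**Working it through.** The article gives no engagement count, expected engagement effect or reply rate, so there is no figure to reproduce. The check is an illustration with the audience held constant.

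**Inputs from the article**
- Comments are a platform count with no restriction on who wrote them (both Social Media Engagement sections).
- Replying to disagreement is taught in the intervention phase (Intervention; Table 1, Session 6) and left to usual practice before it (Study Design).

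**Assumptions, none given in the article**
- Platform totals include the author's own replies.
- Own replies per audience comment are r0 in the control phase and r1 in the intervention phase.

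**Formula.** Let A be audience comments per post, the same in both phases. The platform total is A + rA = A(1 + r). The intervention-to-control ratio is A(1 + r1) / [A(1 + r0)] = (1 + r1)/(1 + r0), and A cancels. If the audience does change by a true factor t, the observed ratio is t(1 + r1)/(1 + r0), so the distortion multiplies the true effect.

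**Results with an unchanged audience (true ratio 1.00)**

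| r0 | r1 | Comment ratio |
|---|---|---|
| any | same as r0 | 1.00 |
| 0 | 0.25 | 1.25/1.00 = 1.25 |
| 0 | 0.5 | 1.50/1.00 = 1.50 |
| 0.1 | 0.25 | 1.25/1.10 = 1.14 |
| 0.1 | 0.5 | 1.50/1.10 = 1.36 |
| 0.1 | 1.0 | 2.00/1.10 = 1.82 |
| 0.25 | 0.5 | 1.50/1.25 = 1.20 |
| 0.5 | 1.0 | 2.00/1.50 = 1.33 |

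The curriculum text concerns disagreement. If promotores answer only opposing comments, once each, r cannot exceed the share of audience comments that are opposing. That makes the larger values of r1 less likely.

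**The other metrics.** Impressions are defined as users who view a post, so a reply hardly moves them. A reply is not a like or a share, so those counts are not raised by replying as such.

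**After the fix.** With own replies removed in both phases, the ratio is A/A = 1.00 when the audience does not change.

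**The case against.** The strongest reply is that this is an ordinary data-cleaning rule. The article condenses a fuller protocol, a statistical analysis plan may exist, and an exclusion of own comments may already be written there. The article also names the audience as the target and analyses audience responses separately. This stands in part: nothing printed is false, and the inclusion of own replies in platform totals is an inference. But the article does print the scoring rule, and that rule points to unrestricted platform counts. The separate content analysis leaves the count outcome as it is.

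A second reply is that the Session 6 task is to plan a strategy, not to post public replies, so r may change little or not at all. That also stands. The effect is possible, not certain.

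A reader might infer more than the article supports, in four ways:
- **Peers and the study account.** Table 1 has promotores join a group and follow the study's account. It does not say that the account or cohort members like, comment on or share live posts, and the peer feedback it describes concerns drafts. Inflation by this route is only a possibility.
- **All engagement metrics.** Without that route, the comment count is the exposed component.
- **Narrative against standard posts.** Trained promotores publish both kinds, and nothing indicates that narrative posts draw more disagreement.
- **A false-positive rate.** Any such figure would need invented post counts, comment means and reply rates, and would have to be run under the planned mixed model. None is offered here.

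**Conclusion.** The point holds for the comment count. As the rule is written, comments are not restricted to the audience, and the training targets a behaviour that can add to them from crossover onward. If platform totals include the author's replies and training raises replying, the comment ratio is inflated by (1 + r1)/(1 + r0): 14% to 36% for r rising from 0.1 to between 0.25 and 0.5, and nothing if replying does not change. The values of r are assumptions, and the article neither supports nor excludes them.

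The article does not establish that the training raises the engagement score, only that it may. Vaccination-related decision-making, the primary outcome under Sample Size, comes from surveys and is not affected. This is a correction to a listed, non-primary outcome. It is worth making because it is cheap and the model cannot make it afterwards.

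**What to change.** In both Social Media Engagement sections (Outcomes and Data Analysis), define the comment count as comments by accounts other than the posting promotor, in control and intervention phases alike. Where they can be identified, also exclude other enrolled promotores, study staff and the Dime La VerDAD account. Report promotor replies separately as a communication-practice or fidelity measure, since they are of interest in their own right. Present the unfiltered totals as a sensitivity analysis.

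Filter likes and shares in the same way only where account-level data are available. The article does not say that the identity of people who react or share is captured, and its confidentiality section limits what is collected.

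The cost is a few lines of wording and a filter on comment authors. The content of posts and audience responses is already to be analysed, and under Trial Status data collection is not complete, so the rule can still be set. The small downside is that platforms giving totals only cannot be filtered. Their counts should be identified as unfiltered.

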Despite this work, there remains a limited understanding of how health information circulates and is interpreted within Spanish-language social media networks. In particular, few studies have examined how inaccurate or misleading health information is encountered in these settings or how responses grounded in scientific evidence are received by community members. In addition, it remains unclear which communication approaches are most effective in promoting engagement, recall, and informed decision-making in real-world social media environments. Addressing these gaps is essential for developing effective and scalable approaches to communicating evidence-based health information within Spanish-speaking communities.

To address these gaps, we developed Dime La VerDAD (“Tell Me the Truth”: Verify, Debunk, and Disseminate), a structured, community-engaged social media training program designed to support promotores de salud in disseminating reliable, evidence-based information about respiratory virus prevention. The program is grounded in principles of health communication and is designed to build practical skills in identifying inaccurate health claims, developing clear and accessible messages, and engaging effectively with social media audiences.

This study will evaluate the implementation and effectiveness of the Dime La VerDAD program using a stepped-wedge design across community-based cohorts. Specifically, it will characterize how health information is shared and interpreted within Spanish-language social media networks, evaluate whether a structured, evidence-based communication training program improves the quality and reach of health messaging, and assess whether narrative-based approaches differ from standard informational content in influencing engagement and vaccination-related decision-making. We hypothesize that promotores will be perceived as trusted messengers and that narrative-based posts will result in greater engagement and improved decision-making in favor of recommended immunizations.

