### Interim Analyses

Interim analyses will be conducted at prespecified time points to summarize implementation metrics, engagement patterns, and participant feedback. These analyses will be used to monitor feasibility and fidelity of the intervention. Interim findings will inform operational adjustments (e.g., scheduling or delivery format) but will not be used to modify primary outcomes or determine early trial termination.

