### Risks and Protections

Risks associated with participation are expected to be minimal and may include potential discomfort discussing health-related topics or concerns related to sharing information on social media. Participants will be informed that they may skip questions or decline to participate in any study activity. The study team will take steps to minimize risks by emphasizing voluntary participation and protecting confidentiality.

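### Engagement is tested on counts that ignore tone, and the planned agreement coding is used to predict those counts, not to split them

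*Protocol article*

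**What the plan says.** The Outcomes section on social media engagement collects impressions and "indicators of interaction such as likes, comments, and shares". The matching Data Analysis section repeats this ("Social media engagement will be quantified using platform-derived metrics, including impressions, likes, comments, and shares") and adds that "Count-based outcomes will be analyzed using Poisson or negative binomial regression models". Neither section divides the counts by tone or by agreement with the post.

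The Background hypothesis makes more engagement the favourable direction for one post format: "narrative-based posts will result in greater engagement and improved decision-making in favor of recommended immunizations".

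The Data Analysis section also plans to extract features from posts and audience responses with language models: "These characteristics will include sentiment, discussion of personal experience, presence of scientific evidence, and patterns of agreement or disagreement". It then enters these features as independent variables in models of engagement. A further paragraph says the content of audience responses will be examined as well as volume, but it names no outcome variable and no model.

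Opposition is foreseen. Table 1, Session 6, gives the assignment "Develop a strategy to address responses from people with opposing views". The Sample Size section names survey-reported vaccination decision-making as the primary outcome.

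**The concern.** Posts about vaccines can draw comments because readers agree or because they object, and a total comment count treats the two alike. If narrative posts provoke more objection than standard posts, the count model returns a rate ratio above 1, which is the direction the hypothesis predicts.

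This matters most for the comparison of formats. Under Table 1, each promotor posts both standardized content and a personal infographic with a narrative caption to the same network. The surveys can tell the two formats apart only through what members report seeing and recalling. Engagement is recorded post by post, so it is the most direct evidence on narrative versus standard content, and its meaning needs to be clear.

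The role given to the coding adds a second problem. Agreement or disagreement in the responses is read from comments, and comments are part of the outcome. Using it to predict comment counts is partly circular.

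**Working it through.** The plan states no figure on this point, so there is nothing to reproduce. The check has two parts.

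**1. Reading the sections together**

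- Outcome: counts of impressions, likes, comments and shares, with no split by valence.
- Favourable direction: more engagement for narrative posts (Background).
- Coded features: sentiment, personal experience, scientific evidence, agreement or disagreement, taken from posts and from responses.
- Named use of the features: independent variables.
- Response-content analysis: planned, with no outcome or model named.

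No named model therefore has opposing or supportive comments as its outcome. A post with no comments also has no response-derived agreement value, so that predictor is defined only where the outcome is above zero.

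Personal experience is in the same feature list as response agreement. If both enter one model, the narrative coefficient is adjusted for something the post itself may have caused. The article does not say whether they would.

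**2. How far the total can move**

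The documents give none of these inputs. All are assumptions:

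- h = share of comments on standard posts that are opposing
- k = multiplier on opposing comments for narrative posts
- s = multiplier on all other comments (called supportive here)

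The rate ratio for total comments per post is

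RR = (1 − h) × s + h × k

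With k = 2 (opposing comments double):

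| h | s = 1 (others unchanged) | s = 0.9 (others fall 10%) |
|---|---|---|
| 5% | 0.95 + 0.10 = 1.05 | 0.855 + 0.10 = 0.955 |
| 10% | 0.90 + 0.20 = 1.10 | 0.81 + 0.20 = 1.01 |
| 20% | 0.80 + 0.40 = 1.20 | 0.72 + 0.40 = 1.12 |
| 30% | 0.70 + 0.60 = 1.30 | 0.63 + 0.60 = 1.23 |
| 50% | 0.50 + 1.00 = 1.50 | 0.45 + 1.00 = 1.45 |

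In the left column the whole rise comes from opposing comments. In the right column the total passes 1 where 0.9 + 1.1h = 1, so h = 0.1/1.1 = 9.1%. Above that share, the total rises while supportive response falls.

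At h = 30% and s = 0.9, the plan's count gives 1.23. Separate outcomes would give 0.90 for supportive and 2.0 for opposing comments.

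**The case against.** The strongest reply is that the authors already distinguish volume from quality. They code sentiment and disagreement in responses and say they will examine response content to learn about the quality of interaction as well as its extent. An article may leave the model for that to a fuller document. This stands in part: valence is not ignored, and the missing model alone would not be a finding. What remains is a choice the article does state, namely that features of the responses predict a count that includes those responses.

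Several stronger readings are tempting but are not supported:

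- *Backlash would be counted as success.* No engagement success criterion is set, the primary outcome is survey decision-making, and the Background hypothesis also requires improved decision-making. The supportable wording is that backlash could be misread on the volume measure.
- *Interim monitoring would take hostility for good uptake.* The interim analyses "summarize implementation metrics, engagement patterns, and participant feedback". Engagement patterns are not defined there as counts, participant feedback is included, and the purpose is feasibility and fidelity. Post-intervention focus groups also ask about community responses. Risks and Protections mentions "concerns related to sharing information on social media" but not hostile replies.
- *The curriculum predicts harm or misinforming comments.* Session 6 prepares promotores for dissent, to be handled constructively. It does not call dissent harm.
- *The total count should be dropped.* A programme that addresses inaccurate claims may want sceptics to engage, so total comments remain a legitimate outcome.

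The size is also open to challenge: at a 5% opposing share the effect is slight (1.05) or reversed (0.955).

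**Conclusion.** The point holds in a limited form. The count test of the narrative hypothesis cannot separate supportive from opposing comments, and the coding that could separate them is given a partly circular role as a predictor. A total-comment rate ratio above 1 could come wholly from opposing comments.

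Under the assumed doubling of opposing comments, the ratio is 1.05 to 1.50 with other comments unchanged and 0.955 to 1.45 with other comments down 10%, across opposing shares of 5% to 50%. The true share and multipliers are unknown, and the calculation covers comments only. The primary analysis is not affected. This is a low-cost improvement to how a secondary comparison is read.

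**What to change.** In Data Analysis, Social Media Engagement:

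1. Use the coding already planned to classify each comment as supportive, neutral or opposing.
2. In the narrative versus standard comparison, model the three classes as separate count outcomes alongside total comments, with the same Poisson or negative binomial mixed model. Report the opposing-comment rate ratio in its own right.
3. Do not use valence derived from responses as a predictor of comment counts. Features of the post itself, such as narrative or cited evidence, can stay as predictors.
4. Report likes, shares and impressions separately, and describe shares and impressions as reach of unknown valence, since a share count does not show why the post was shared.

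The cost is some wording and refitting a planned model to comments that are already to be coded. The downsides are smaller counts per class, hence wider intervals, and some classification error. Trial Status reports that data collection is not complete, so the split can still be fixed in advance.
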